### Healthy lifestyle program

The HLP includes access to a list of free online resources, a health coach, and physical activity monitoring (step count, time spent in various cadence bands, and sedentary time) using the Garmin vívofit 4 activity tracker and recording and monitoring of goals with the goal-setting app. Considering that gyms are high risk in the COVID-19 era, we will provide participants with links to online exercise and yoga classes, which they can do in their home with minimal equipment. We have also created two 30–40-min bootcamp classes. Participants will be encouraged to follow the bootcamp class twice a week and take a yoga class once a week. Once they are comfortable, participants will be encouraged to take other online fitness classes. Those who have a medical contraindication to moderate exercise (chronic heart failure, angina, history of myocardial infarction) will be recommended to use only the yoga resources for exercise. All participants will be assigned a health coach to facilitate the transition into using community resources to meet their goals. The health coach will provide feedback, encouragement, and suggestions for increasing activity via weekly interactions throughout the HLP.

### Goal management training

The intervention group will participate in GMT, a standardized cognitive rehabilitation program, which will be provided per the manual. It consists of 9 online sessions, once per week, for two hours [41]. Participants will be given homework to complete between the sessions. There are five steps in GMT [28]. In stage 1, participants are asked to stop and ask what task they are trying to accomplish. They select their goals in stage 2, and these goals are partitioned into smaller steps in stage 3. Stage 4 involves encoding and retention of goals and steps. In stage 5, participants monitor their outcomes to make sure they align with their original goals [28].

### Outcome measures

Refer to Table 1 for a list of outcome measures that will be administered in this study.

**Table 1 Tab1:** Outcome measures

Outcome	Measure	Value
*Confirmatory outcomes*		
Primary 1: uptake of the recommendations for physical activity	Number of physical activity-weeks. Recorded by Garmin VivoFit 4	Number of weeks in which physical activity guidelines are met (150 min of moderate to vigorous activity in bouts of 10 min) [42]
Primary 2: uptake of the recommendations for social activity	Number of social activity-weeks. Recorded by pictures provided by participants	Number of weeks in which at least one social activity was attended
*Explanatory outcomes*		
Achievement of personal goals	Goal attainment scaling [40, 43] Recorded on the goal-setting app	N and diversity of goals set and met
Physical activity pattern	Daily step counts, time spent in cadence bands for moderate (100 steps/min) and vigorous (130 steps/min) intensity [44], sitting time. Recorded by the Garmin VivoFit 4	Trajectory of weekly cumulative step counts (rising, stable, falling) Trajectory of weekly cumulative sitting time (rising, stable, falling)
General Health perception, sleep, distress, pain, fatigue, depression, anxiety, quality of life	Visual Analogue Health States [45]	0–10 for each
*Downstream health outcomes (platform measures)*		
Mood	RAND-36 Mental Health Inventory [46]	0–100
Energy/fatigue	RAND-36 Vitality [46]	0–100
Physical function	RAND-36 Physical Function Inventory [46] and five-repetition sit-to-stand test [47]	0–100; time in seconds
Performance based-report cognitive ability	Brief Cognitive Ability Measure (B-CAM) [48]	0–35 English / 42 French
Self-report cognitive ability	Communicating Cognitive Concerns Questionnaire (C3Q) [37]	0–36
Health related quality of life	EuroQol Five Dimensions Questionnaire (EQ-5D) [49], Patient Generated Index [50, 51]	0–1; 0–100
Improved vascular risk profile	Framingham Cardiovascular Disease Risk Score [52, 53]	Probability of stroke
Social network size	Social network size and quality [54]	0–100

### Confirmatory outcomes

The main confirmatory outcome will be physical activity and social activity adherence to the HLP, hypothesized to be greater with GMT priming. The former will be measured by counting the number of weeks that physical activity adherence targets were met, i.e. 150 min per week of moderate to vigorous exercise, accumulated in bouts of at least 10 min [42]. This outcome will be assessed continuously with the activity monitor (*Garmin VivoFit 4)*. The latter adherence outcome will be the number of documented social activities per week captured through self-report with confidential photo validation. For example, if they attend a yoga class or a painting class, they can take a picture of the yoga studio or art studio and send to a secure email address. A research team member will record the details of the activity and then the picture will be deleted. Participants will be instructed to not take pictures of other people and are not obliged to appear in the picture.

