**Methods:**

Brain Health Now cohort participants with cognitive difficulties or are not aging successfully are eligible. All participants will be given health resources, a health coach, a goal-setting digital application, and access to an online goal-setting workshop. The intervention group will participate in nine 2-h goal management training sessions and then will enter the healthy lifestyle program. Control participants will enter the healthy lifestyle program directly. A total sample of 100 participants will participate for 12 months. The main outcome is adherence to the healthy lifestyle program, defined as the number of weeks where physical activity adherence targets were met (150 min per week, measured with an activity monitor). Weekly social activities will be captured via self-report with confidential photo validation. We will send weekly health state reports to the participants. Downstream outcomes include cognitive ability, health-related quality of life, mobility, vascular risk profile, and social network size. We will analyze the data using a linear regression model.

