### Sample size

Sample size calculations were based on estimates of usual rates of adherence to physical activity for Canadian adults estimated at 10–20% of the time [68], translating to approximately 9 of 52 weeks for the control group and a desired 22 weeks (50% of 43 weeks) in the GMT priming group, which is the targeted adherence rate for interventions for cardiovascular risk factor improvement [69]. As we expect that elements of the HLP program will lead to some activity improvement in the control group (+ 4 weeks), we will power our study to detect a minimum difference of 9 activity weeks between groups over 43 weeks with an estimated SD of 11 weeks. With adjustment of the variance (standard deviation) by 15% to account for dropouts and the need to impute data, this yields an effect size of 0.71 [70]. For 90% power and risk of Type I error of 0.05, the required number of people is 38 participants per group. We will therefore target a total sample of 100 (50 per group) to account for uncertainty in our sample size assumptions and incomplete data. This sample size will also be sufficient to permit other statistical models to be used in the case of non-normality, such as ordinal regression.

Taking advantage of the trial being embedded in the cohort, we will also compare platform outcomes for trial participants with platform outcomes for people who were eligible for the trial but not enrolled, including those at other sites, providing information about how the HLP with or without GMT compares to tailored brain health risk recommendations alone.

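### The protocol article treats physical activity-weeks as the single main outcome in some places and lists two confirmatory primaries in others, with no rule for success

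*Protocol article*

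**What the plan says.** The places that bear on the primary outcome in the Protocol article are these.

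- **Abstract, Methods:** "The main outcome is adherence to the healthy lifestyle program, defined as the number of weeks where physical activity adherence targets were met". Social activity appears there only as something to be recorded each week.
- **Outcome measures, Table 1:** under the confirmatory heading there are two rows, "Primary 1: uptake of the recommendations for physical activity" and "Primary 2: uptake of the recommendations for social activity".
- **Confirmatory outcomes:** "The main confirmatory outcome will be physical activity and social activity adherence to the HLP". Two separately measured variables are put into one singular outcome.
- **Statistical analysis:** a linear model, with a Poisson fallback, is described for physical activity-weeks. No other outcome has a model named for it.
- **Sample size:** the difference and SD are in physical activity-weeks, and the result is "For 90% power and risk of Type I error of 0.05, the required number of people is 38 participants per group". No effect or SD is given for social activity.

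The social outcome itself has two definitions. Table 1 counts the weeks with one or more social activities. The Confirmatory outcomes section describes a weekly count of documented activities.

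**The concern.** Which outcome is primary, and what result would confirm the hypothesis, should have one answer. Here the abstract, the named model and the sample size point to a single primary, while Table 1 and the Confirmatory outcomes text point to two.

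The gap matters most if the outcomes disagree. Suppose physical activity-weeks show no difference and social activity favours goal management training. On the abstract, the trial has missed its main outcome. On Table 1, a confirmatory primary has succeeded, although it has no power calculation and no settled definition. The same data could be reported as a negative or a positive trial, and the choice could be made after seeing the results.

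**Working it through.** **The plan's own figure.** The inputs, all from Sample size, are a difference of 9 weeks, an SD of 11 weeks, a 15% inflation, 90% power and "risk of Type I error of 0.05". Sidedness is not stated; I assume two-sided.

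- Effect size: 9 / (11 × 1.15) = 0.711, which reproduces the stated 0.71.
- n per group = 2(1.960 + 1.282)² / 0.71² = 41.7, so 42 (43 with the t distribution). One-sided gives 34 or 35.
- The stated 38 is therefore not reproduced from 0.71. It is reproduced with the t distribution if the variance rather than the SD is inflated by 15%: d = 9 / (11 × √1.15) = 0.763. This is a separate matter, and the planned 50 per group covers both versions.

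The whole calculation concerns physical activity-weeks. The three possible readings of the primary then compare as follows.

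**Reading 1: physical activity-weeks is the single primary.** The error is 5%. At 50 per group and d = 0.71, the non-centrality is 0.71 × √(50/2) = 3.55, and power is Φ(3.55 − 1.960) = 94.4% (94.0% with t). This agrees with the abstract and the sample size but contradicts Table 1 and the Confirmatory outcomes section.

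**Reading 2: either outcome suffices, each at two-sided 0.05.** With independent tests the family-wise error is 1 − 0.95² = 9.75%, and it can never exceed 0.05 + 0.05 = 10%. With correlated test statistics it is 1 − P(|Z₁| < 1.96 and |Z₂| < 1.96) under a bivariate normal. The document gives no correlation, so this is a range:

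| Assumed correlation | Family-wise error |
|---|---|
| 0 | 9.75% |
| 0.3 | 9.5% |
| 0.5 | 9.1% |
| 0.7 | 8.4% |
| 0.9 | 7.0% |

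Counting only false wins in favour of the training, it is 4.9% at correlation 0 and 4.5% at 0.5, against a nominal 2.5%.

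**Reading 3: both must succeed.** A false claim requires rejecting at least one true null at 0.05, so the error is at most 5%. Power for the joint claim cannot exceed power for physical activity alone, and cannot be computed because the social outcome has no effect or SD. As an illustration only, 90% on each with independence gives 0.90 × 0.90 = 81%.

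**Candidate repairs at 50 per group, d = 0.71.**

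- Fixed sequence, physical activity first: error at most 5%, power for physical activity 94.4% (94.0% with t), no change in N.
- Split 0.025 / 0.025: error 1 − 0.975² = 4.94% if independent and at most 5% otherwise. Power for physical activity is Φ(3.55 − 2.241) = 90.5% (89.7% with t). Reaching 90% needs 50 (normal) or 51 (t) per group.

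**The case against.** A reader might infer that the trial's real type I error is 9 to 10% rather than 5%. The document does not support that, for three reasons.

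- No sentence says that success on either outcome is enough. The singular noun and the word joining the two outcomes can equally mean that both are required, and then there is no inflation.
- The 0.05 is an input to the physical activity sample size. It is not put forward as a trial-wide error rate, so no family-wise claim is being broken.
- Even under an either-one rule, 9 to 10% holds only for two-sided tests and correlation up to about 0.5. The Confirmatory outcomes section uses a yoga class as an example of a social activity, and yoga is also part of the Healthy lifestyle program, so positive correlation is plausible. Its strength is unknown, and the Discussion says that trackers underestimate yoga.

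A reader might also infer that no testing order exists. This is a condensed article, and testing order is commonly left to an analysis plan that is not shown, so its absence here proves nothing.

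Finally, there are signs of a lead outcome: the abstract, the model and the sample size all concern physical activity-weeks, and Table 1 numbers it first. That makes an either-one rule the less natural reading, but the numbering is not described as a hierarchy.

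All of this stands, and it makes the error figure conditional. It does not remove the contradiction. An analysis plan could agree with the abstract or with Table 1, but not with both.

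**Conclusion.** The concern holds as an internal contradiction: one main outcome in the abstract, the named model and the sample size, against two confirmatory primaries in Table 1 and the Confirmatory outcomes section, with the success rule left open. This rests on the text alone.

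Its size depends on the intended rule. If either outcome counts, the family-wise error is up to about 10%, assuming two two-sided 0.05 tests and a correlation that the document does not give. If both are required, the error is controlled, but the stated 90% power does not describe the claim. If physical activity is the single primary, neither problem arises and only the labels are wrong. The conflicting definitions of the social outcome add to the problem under any rule that tests it.

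**What to change.** 1. Name physical activity-weeks as the single primary outcome, tested at two-sided 0.05. This follows the abstract and the sample size.
2. Test the social outcome as confirmatory, at two-sided 0.05, only if the first test is significant.
3. Make the abstract, Table 1 and the Confirmatory outcomes section say this in the same terms.
4. Choose one variable for the social outcome, either weeks with any activity or a count of activities. The sequence cannot be run until this is settled.

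The study is described as ongoing, so the change should be dated and made before anyone sees results by group.

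The cost is wording and an amendment, with no extra participants. The downside is that the social outcome cannot be claimed as confirmatory if physical activity fails. If the investigators want each outcome to stand alone, a 0.025 / 0.025 split is workable: it keeps about 90% power for physical activity at the planned 50 per group and d = 0.71. If they want both to be required, the sample size section needs an effect and SD for the social outcome and a power figure for the joint claim.

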### Explanatory outcomes

Principles of Goal Attainment Scaling [40, 43] will be used to assist with goal-setting. Participants will use the digital goal-setting application developed by our team to set at least three goals, actions for each goal, how difficult the goal will be to achieve, and the importance of the goal. Weekly and monthly reminders will be sent to participants to determine their progress in achieving their goals.

Physical activity patterns including daily step counts, time spent in cadence bands for moderate (100 steps/min) and vigorous (130 steps/min) intensity [44], and sitting time will be recorded using the Garmin VivoFit 4 activity tracker. Garmin activity trackers have been widely used to measure step count, physical activity, and sedentary time and have established validity and reliability [55].

The MyHealth app will be used to send visual analog scale health states questionnaires to the participants. A questionnaire will be sent every week and the participants will have the 48 h to respond to it. There are 8 questions about their level of pain, anxiety, depression, sleep, distress, fatigue and health perception using the validated Visual Analog Scale [45]. See Fig. 2 to view the questionnaire.

**Fig. 2 Fig2:**
[figure not shown]
Visual analog health states questionnaires

### Downstream measures

The downstream measures will be administered during their regular ABHN study assessments by a blinded trained research coordinator. The ABHN visits are scheduled every 9 months so all of the participants in the trial will have at least one visit during the period of the trial and one after the trial is completed. Due to COVID-19 restrictions, these assessments are conducted virtually.

The EuroQol Five Dimensions Questionnaire (EQ-5D) measures five aspects of health-related quality of life, including mobility, self-care, usual activities, pain and discomfort, anxiety and depression. There is evidence of construct and convergent validity, as well as responsiveness to treatment and changes in health status [56]. The physical functioning (10 items), mental health (5 items), and vitality (4 items) subscales of the RAND-36 will be used to measure aspects of health-related quality of life [46]. The RAND-36 has good to acceptable internal consistency, construct validity, and responsiveness [56]. It has been used widely in the literature [57]. Physical function will also be assessed using the five-repetition sit to stand test, which has been used to predict fall risk among people living with HIV [58].

We will measure cognitive ability using the Brief Cognitive Ability Measure (B-CAM), a brief computerized cognitive test developed by our team using Rasch analysis where higher scores reflect better cognitive ability [32, 59]. The B-CAM includes tests of reaction time, response inhibition [60], memory and learning, working memory [61], visuospatial memory [62], verbal fluency, and executive function [63, 64]. Self-reported cognition will be assessed using the Communicating Cognitive Concerns Questionnaire (C3Q), an 18-item questionnaire that estimates the frequency of cognitive difficulties among people living with HIV on a three-point scale with higher scores reflecting less frequent cognitive difficulties [37, 65].

### Data collection

The data of participants included in the study will be stored in a secure server held at the McGill University Health Centre Research Institute, accessible only to the research team. The data will be stored in conjunction with the participants’ anonymous codes. Any participant’s identification will take place through a separate information source and external to the system, making it possible for the research team to reconstruct the correspondence between the anonymized data and the participants enrolled in the study. Data backup will be made daily and automatically in order to properly secure data storage. The principal investigator will assure the quality of computerized data for this study. Those collecting and analyzing the data will be kept blind to group assignment.

### Ethical considerations

All procedures will be in accordance with the Helsinki Declaration. Any amendments to the study protocol will be submitted for review to the research ethics board. Adverse events will be immediately reported to the research ethics board and the participants will be directed to obtain treatment if needed. Protocol violations or deviations will be reported to the principal investigator. Protocol exemptions, violations, and deviations will be logged. All participant-related information including the questionnaires, evaluation forms, and reports will be kept strictly confidential. All records will be kept in a secure, locked location and only research staff will have access to the records. Participants will be identified only by means of a coded number specific to each participant, and a participant letter code. All computerized databases will identify participants by numeric codes only and will be password protected. Participants will consent to have their MyHealth app data stored with DataRiver in the informed consent form prior to the collection of any research data. DataRiver will destroy all the data and wipe hard drives clean and the storage solution as well, once the data has been transferred to the principal investigator and the study is closed. Upon request, clinical information may be reviewed by or released to auditors, funders, or regulatory agencies. Participants will be given the option to withdraw from the study at any time with no effect on their care or ability to remain in the cohort study.

### Statistical analysis

The analysis assumes that the distribution of physical activity-weeks at the end of the study period will be near normal, permitting a linear regression model; if not, a Poisson model can be used. Both intention-to-treat, with imputation and sensitivity analyses, and per protocol analyses will be conducted. Intention-to-treat will address the benefit of offering GMT as a service to all with need, while the per protocol analysis will address the benefit to those who are able to adhere to the program and will help identify characteristics (including sex and gender) of those most able to benefit. We will follow the Sex and Gender Equity in Research (SAGER) [66] guidelines and will present study data disaggregated by sex and gender. To address bias resulting from missing data, we will conduct multiple imputation on the data for outcomes with sufficient data [67].

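### The Poisson fallback for physical activity-weeks conflicts with the plan's own SD of 11: used with ordinary standard errors it would have a type I error of about 40–52% instead of 5%

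*Protocol article*

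**What the plan says.** The Statistical analysis section of the protocol article makes linear regression the main analysis of physical activity-weeks, provided their distribution is close to normal: "permitting a linear regression model; if not, a Poisson model can be used". It mentions no scale parameter, robust variance or overdispersed alternative. Table 1 defines the outcome as "Number of weeks in which physical activity guidelines are met", so it is a count with an upper limit set by the weeks observed.

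The Sample size section gives the planning figures. Usual activity is "approximately 9 of 52 weeks for the control group", and the healthy lifestyle program is expected to add 4 weeks, which makes 13. The GMT group is planned at 22 weeks. The difference to detect is 9 weeks "over 43 weeks with an estimated SD of 11 weeks". The same section remarks that the sample is large enough to "permit other statistical models to be used in the case of non-normality, such as ordinal regression".

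**The concern.** A Poisson model fixes the variance equal to the mean, and its ordinary standard errors rely on that. Activity-weeks are a sum of weekly successes within a person. Some people meet the target nearly every week and others hardly ever, so the person totals vary far more than a Poisson count would. The plan's own SD says as much.

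If the fallback were applied as named, intervals would be much too narrow and the test on a primary outcome would reject far too often. A trial of an ineffective intervention could then easily be reported as positive.

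**Working it through.** **Inputs, all from the Sample size section.** SD 11 weeks, so variance 121. Control mean 9 + 4 = 13. GMT mean 22; midpoint (13 + 22)/2 = 17.5. Difference 9. Target 50 per group. Alpha 0.05, taken as two-sided because the article does not say.

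**The plan's own figures.** Inflating the SD by 15% gives 11 × 1.15 = 12.65, and 9/12.65 = 0.71, the stated effect size. The stated 38 per group does not follow from 0.71, which needs 42 (normal approximation) or 43 (t distribution) for 90% power. It does follow if the 15% is applied to the variance: SD 11.80, effect size 0.76, 38 per group by the t distribution. That is a separate matter: the target of 50 per group still gives about 94% power at 0.71, and nothing below depends on it.

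**SD implied by a Poisson model.** This is the square root of the mean: √13 = 3.6 and √22 = 4.7 weeks, against the planned 11. Independent weeks out of 43 would give a binomial SD of about 3.0 and 3.3, so an SD of 11 implies strong within-person correlation.

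**Size of the error.** Dispersion φ = variance/mean. Model-based Poisson standard errors are too small by √φ, and interval width is 1/√φ of what it should be. The true two-sided size of a nominal 5% Wald test is 2 × (1 − Φ(1.96/√φ)). Each row takes one mean for both arms, as under the null.

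| Common mean | φ | SE too small by | Interval width, share of correct | True type I error |
|---|---|---|---|---|
| 13 | 121/13 = 9.3 | 3.1 | 33% | 52% |
| 17.5 | 121/17.5 = 6.9 | 2.6 | 38% | 46% |
| 22 | 121/22 = 5.5 | 2.3 | 43% | 40% |

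**Simulation under the null.** Outcomes were drawn from a beta-binomial on 0 to 43 weeks and from a negative binomial, SD 11, with 38 and 50 per arm and 20,000 trials per setting. The plain Poisson test rejected in 52–53% of trials at mean 13, about 46% at 17.5 and 40% at 22, the same at both sample sizes.

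Over these means and a mean of 9, the alternatives gave:
- t test (the unadjusted linear model): 4.6–5.3%
- quasi-Poisson: 4.7–5.4%
- Poisson with sandwich standard errors: 5.3–6.6%

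**Sensitivity to the SD.** With the inflated SD of 12.65, φ is 12.3 at mean 13 and 7.3 at mean 22, and the type I error 58% and 47%. Overdispersion disappears only if the SD falls to about 3.6–4.7 weeks.

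**The case against.** The strongest reply is that the inflation is conditional. Linear regression is the planned analysis, the abstract names nothing else, and it is sound. Harm needs three steps: the distribution is judged non-normal, Poisson is chosen, and no dispersion correction is applied. The article says only that Poisson may be used, and the method for standard errors is a detail that an analysis plan, not shown here, could supply. This stands as a limit on the claim. It does not remove it: Poisson is the only fallback named in the analysis section, and in its ordinary form it conflicts with figures given in the next section.

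A reader might infer several stronger points that the article does not support.

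- *The fallback is bound to be triggered.* A normal distribution with mean 13 and SD 11 would put about 12% of its mass below zero, so close normality is unlikely in the control arm. It is not excluded. In a beta-binomial over 43 weeks with SD 11, skewness is 0.72 at mean 13 but −0.04 at mean 22, and the article sets no threshold for near normal.
- *The model would be picked to suit the result.* The Data collection section keeps those who analyse the data blind to group, and none of the 40–52% comes from the selection step.
- *Ordinal regression is a second, competing fallback.* The Sample size section gives it only as an example of what the sample size permits.
- *A null trial has an even chance of significance, with intervals a third of their proper width.* Both figures hold near a mean of 13. At 22 they are 40% and 43%.

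**Conclusion.** The point holds in conditional form. An ordinary Poisson fallback is incompatible with the planned means and SD, and using it would raise the type I error for physical activity-weeks from 5% to about 40–52%. The exact range rests on the planning SD of 11, common means between 13 and 22, a two-sided test and model-based standard errors. The direction does not: any SD well above 5 weeks gives an excess. The result is the same at 38 and 50 per arm, so a larger sample would not cure it. The article does not support reading this as a fault in the main analysis, since linear regression keeps about 5% even with the skewed distributions simulated.

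**What to change.** Replace the plain Poisson fallback in the Statistical analysis section by one of two statements:

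1. Linear regression with robust standard errors will be used whatever the shape of the distribution. This is the simpler choice, because the linear model already holds its level under the planning assumptions.
2. Any count model will use an overdispersion-adjusted or robust variance: quasi-Poisson, Poisson with sandwich standard errors, or a beta-binomial or quasi-binomial model that respects the upper limit on weeks.

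The cost is one sentence, with no extra data and no change in sample size. Under the second option, intervals would be about 2.3 to 3.1 times as wide as an uncorrected Poisson model would print. That is their correct width, so no real precision is lost.
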